The biggest barrier to HIV remission and cure in children and adults is the presence of latent HIV reservoirs (resting memory T cells and other sites, which contain integrated proviral DNA) [23]. These reservoirs usually reach a set point within the first 2 months of infection and serve as predictors of long-term HIV control [10,24]. When ART is discontinued, these HIV latent reservoirs allow for viral rebound to occur [25,26]. However, if cART is initiated during the acute phase of infection, it is possible to preserve the cluster of differentiation 4 (CD4) T cells and decrease the size of HIV reservoirs [24,27,19]. A period of drug-free remission may then be possible [21]. The French National Agency for Research on AIDS Visconti trial identified 14 adults that were treated during early acute infection and were able to maintain undetectable viral levels for several years after discontinuing cART [28]. Unfortunately, cART initiated after HIV has become established and is not associated with a limit in viral reservoir size or attainment of remission after cessation of cART [29,30].

Traditionally, adolescents who acquired HIV through sexual transmission have not been included in early treatment studies. Identification and adherence to ART and study visits are some of the many challenges associated with enrolling this population. However, data have shown that adolescents retain more residual thymic tissues than adults, giving them a greater capacity for immune reconstitution and CD4 T cell recovery than adults [31,32]. Therefore, it has been suggested that adolescents may be more responsive to early cART than adults with better chances of obtaining drug-free remission [24]. By identifying this population early and promptly initiating potent ART, with adequate surveillance and dedicated behavioral strategies to retain them in care and optimize ART adherence, it may be possible to significantly limit the size of their latent viral reservoirs and preserve their immune systems. This may enable them to better control HIV persistence for long term and allow them the opportunity to participate in additional strategies to induce HIV drug-free remission or become elite posttreatment controllers.

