### Study Aims

This study aimed to identify and promptly initiate potent cART in acutely or recently established HIV-infected youth aged 12 to 24 years in Los Angeles and New Orleans. We hypothesize that the size of the HIV reservoir and immune activation markers will be different across groups treated with cART: those with acute or recent infection and established infection. We predict that adolescents who are treated early and are virally suppressed during acute or recent infection will have a decreased quantity of HIV reservoirs compared with those with established HIV infection. These youth with low reservoirs and preserved immune systems may be potential candidates for a possible HIV vaccine and additional HIV remission intervention trials.

We expect to recruit youth with acute and recent HIV infection from a large prospective HIV-negative high-risk youth cohort as well as from numerous community clinics. The HIV-negative high-risk youth cohorts are enrolled in a Comprehensive Adolescent Research and Engagement Studies (CARES) partner study, where youth at risk for HIV acquisition are followed periodically for a period of 2 years with point-of-care (POC) periodic HIV testing performed, including fourth generation HIV-1 assays (Alere Determine), GeneXpert qualitative HIV assays (Cepheid), plasma polymerase chain reaction (PCR) assays, and detuned HIV-1/2 enzyme immunoassay. Serial POC testing for syphilis, gonorrhea, and chlamydia are done at the same time points.

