**Control or established (estimated N=36)**				
	4	6	90+	Reactive HIV-1 antibody; positive Western blot with p31 band

^a^Adapted from: Fiebig et al study [11].

**Table 2 table2:** Schedule of evaluations.

Evaluation	Screen	Entry	Week(s)				Month(s)				
			1	2	4	8	4	8	12	18	24
Documentation of acute HIV	X	—^a^	—	—	—	—	—	—	—	—	—
Fiebig staging	—	X	—	—	—	—	—	—	—	—	—
Financial screening	—	X	—	—	—	—	—	—	—	—	—
History	—	X	—	—	—	—	—	—	—	—	—
Physical examination	—	X	X	X	X	X	X	X	X	X	X
Adherence assessment	—	—	X	—	X	—	X	X	X	X	X
Antiretroviral therapy (ART) initiated	—	X	—	—	—	—	—	—	—	—	—
HIV-1/2 enzyme immunoassay fourth generation assay	—	X	—	—	—	—	—	—	—	—	—
HIV-1 genotypic testing	—	X	—	—	—	—	—	—	—	—	—
Urine analysis	—	X	—	—	—	—	—	—	—	—	—
Complete blood count with differential and platelets	—	X	—	X	—	X	X	X	X	X	X
Liver function tests (AST^b^, ALT^c^, GGT^d^)	—	X	—	X	—	X	X	X	X	X	X
Renal function tests (blood urea nitrogen, creatine)	—	X	—	X	—	X	X	X	X	X	X
T cell subsets	—	X	—	X	—	X	X	X	X	X	X
HIV-1 RNA PCR^e^ quantitative	—	X	—	X	—	X	X	X	X	X	X
HIV-1 Western blot	—	X	—	—	X	X	—	X	X	X	X
Hepatitis B and C panel	—	X	—	—	—	—	—	—	—	—	—
Rapid plasma regain	—	X	—	—	—	—	—	—	—	—	—
Gonorrhea/chlamydia PCR of urine, oropharynx, and rectum	—	X	—	—	—	—	—	—	—	—	—
Cytomegalovirus PCR blood	X^f^	X^f^	X^f^	X^f^	X^f^	X^f^	X^f^	X^f^	X^f^	X^f^	X^f^
Pregnancy test	—	X^g^	X^g^	X^g^	X^g^	X^g^	X^g^	X^g^	X^g^	X^g^	X^g^
Reservoir study laboratories (mL)	—	30	10	10	10	10	30	10	30	10	30

^a^Not applicable.

^b^AST: aspartate aminotransferase.

^c^ALT: alanine aminotransferase.

^d^GGT: gamma-glutamyl transferase.

^e^PCR: polymerase chain reaction.

^f^If clinically suspected.

^g^Whenever pregnancy is suspected.

Other potent antiretroviral regimens may be prescribed by the physician based on availability, patient tolerability, and preference. Changes to antiretroviral regimens should be performed when necessary according to HIV management guidelines [41]. Patients who do not tolerate the ART regimens will be prescribed an alternative ART regimen as clinically indicated. The same will occur with subjects who do not achieve viral load remission, and they may be prescribed an alternative ART regimen as clinically indicated.

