### Immune Reservoir Studies

At enrollment, collection of 30 mL of (pretreatment) whole blood is collected and used to determine Fiebig staging through the following tests: (1) HIV-1 POC antibody test (fourth generation assay), (2) HIV-1 WB, and (3) HIV-1 quantitative RNA PCR. In addition, digital droplet PCR to measure full-length and partial HIV combination DNA transcripts are performed at enrollment and for each of the 9 subsequent follow-up visits. These tests allow the evaluation of continued reservoir suppression and sustainability of antiretroviral effect while comparing HIV viral dynamics across subject groups. The total amount of blood to be obtained during each study visit should not exceed 30 mL for youth weighing <50 kg.

The primary study endpoint is 24 months following enrollment, when the amount of cell-associated HIV-1 DNA in 5 million total peripheral blood mononuclear cells (assayed by quantitative digital drop PCR) will be compared between individuals initiating ART at different Fiebig stages: 1/2 versus 3/4 versus 5 versus established infection (Fiebig 6 control arm). We will also have HIV reservoir studies assessed at 4, 8, 12, 18, and 24 months. These data will be important to assess for studies of reservoir decay as well if there is drop out or loss to follow-up or evidence of viral rebound.

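### HIV DNA per 5 million total PBMC mixes HIV DNA per CD4 cell with the CD4 share of PBMC, which the protocol's own reasoning allows to differ by stage group and to change on treatment

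*Protocol article*

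**What the plan says.** The endpoint and its timing are in Immune Reservoir Studies: "The primary study endpoint is 24 months following enrollment", when "the amount of cell-associated HIV-1 DNA in 5 million total peripheral blood mononuclear cells" is compared between those starting treatment at Fiebig 1/2, 3/4, 5 and 6. The same section says that the serial readings also serve to study reservoir decay. The denominator is therefore a stated choice.

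The Background locates the reservoir in "resting memory T cells and other sites, which contain integrated proviral DNA". It says that with treatment in the acute phase "it is possible to preserve the cluster of differentiation 4 (CD4) T cells and decrease the size of HIV reservoirs". It also says that adolescents retain more thymic tissue than adults, "giving them a greater capacity for immune reconstitution and CD4 T cell recovery than adults". That last statement is not limited to those treated early.

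The directional prediction (Study Aims) is that those treated early and suppressed "will have a decreased quantity of HIV reservoirs compared with those with established HIV infection".

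Regression Analysis plans a linear longitudinal model of level and trend, with a stage-by-time interaction, or a longitudinal logistic model if the results mainly divide into detectable and undetectable. CD4 is not among the covariates given as examples. The article states no per-CD4 scale. Table 2 schedules "T cell subsets" and a complete blood count with differential at entry, weeks 2 and 8, and months 4, 8, 12, 18 and 24.

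**The concern.** A fixed number of PBMC holds a variable number of CD4 cells. The exposure under study, stage at treatment start, is expected by the protocol itself to affect CD4 preservation, and treatment is expected to bring CD4 recovery. The composition of the denominator can therefore differ between the groups and move over the 24 months.

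Two results are exposed. In the month-24 comparison, a higher CD4 share in the early group raises its reading at the same infection frequency per CD4 cell, which works against the hypothesis. In the decay analysis, a rising share offsets part of a fall in HIV DNA per CD4 cell. If the rise differs by stage, part of the stage-by-time term reflects CD4 recovery and not the reservoir.

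**Working it through.** The article gives no CD4 share, effect size, SD or power, so there is no planned figure to reproduce. All shares, the contrast and the SD below are assumptions. Only the 36 per cohort comes from the document (36 + 36 = 72, which agrees with the total).

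**Identity.** Let f be the CD4 share of PBMC and d the HIV DNA copies per CD4 cell, with CD4 cells taken as the carriers. Then reading = 5,000,000 × f × d.

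**Month-24 contrast** (control minus early, log10):

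per-PBMC contrast = per-CD4 contrast − log10(f_early / f_control)

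The illustration takes a true per-CD4 contrast of 0.5 log10, SD 0.7, 36 per cohort and two-sided 5%:

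| Share, early / control | Shift (log10) | Per-PBMC contrast | Power |
|---|---|---|---|
| 30% / 30% | 0 | 0.500 | 86% |
| 30% / 27% | 0.046 | 0.454 | 79% |
| 30% / 25% | 0.079 | 0.421 | 72% |
| 30% / 20% | 0.176 | 0.324 | 50% |
| 35% / 20% | 0.243 | 0.257 | 34% |

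Other assumed pairs fall in or close to this range: 40% / 28% gives log10(0.40/0.28) = 0.155, and 45% / 25% gives log10(0.45/0.25) = 0.255. Gaps of 3 to 5 points (rows two and three) cost 0.05 to 0.08 log10. The power column compares two cohorts; the planned comparison divides the early cohort into three smaller groups.

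**Logistic fallback.** At 40% / 28%, 5 million PBMC hold 2.0 and 1.4 million CD4 cells. At equal infection frequency the early group is then the more likely to be detectable.

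**Decay within a group:**

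measured fall = per-CD4 fall − log10(f_month24 / f_baseline)

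For a true fall of 0.5 log10:
- Early, share preserved (30% to 30%): shift 0, reads 0.500.
- Early, recovering from a dip (25% to 32%): shift 0.107, reads 0.393.
- Established (18% to 27%): shift 0.176, reads 0.324.

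**Difference in decay, early minus established,** with equal true falls: artefact = log10(rise ratio, established) − log10(rise ratio, early).
- 30% to 30% against 18% to 27%: 0.176 − 0 = +0.176, so early appears to decay more.
- 25% to 32% against 18% to 27%: 0.176 − 0.107 = +0.069.
- 22% to 32% against 22% to 27%: 0.089 − 0.163 = −0.074, so early appears to decay less.

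**Is the reading total burden instead?** Take 100 PBMC with 30 CD4 and 70 other cells. If the other cells increase to 120, the CD4 share is 30/150 = 20%. The reading falls by log10(0.30/0.20) = 0.176 although no infected cell has been gained or lost. A count in a fixed number of PBMC therefore measures neither frequency per CD4 cell nor total burden.

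**The case against.** The strongest reply is that the hypothesis concerns reservoir size or quantity and not infection frequency per CD4 cell. On that reading, more CD4 cells at the same frequency is a truly larger reservoir, and there is no bias to remove. This stands in part: per-CD4 is not the only legitimate target. It does not settle the matter, because the reading also moves with cells that do not carry the reservoir, as the last calculation shows, and the article does not say which quantity size means.

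Second, the identity assumes that HIV DNA scales with all CD4 cells. The Background names memory cells and other sites, and ties adolescent CD4 recovery to thymic tissue. If the extra CD4 cells are newly produced naive cells with little HIV DNA, the shifts above are too large, and dividing by total CD4 would make the group with more such cells read low. In the scenario of concern that is the early group, so a per-CD4 result could favour the hypothesis. This stands, and it is a reason to show both scales and not to replace one with the other.

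Third, supplementary scales are often left to a full protocol or analysis plan, the results are described as primarily descriptive, and the covariate list is only illustrative. That limits the weight of the point, but the primary denominator is fixed here and a descriptive contrast carries the same mixture.

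A reader might also infer that CD4 preservation in the early group flattens its measured decay. The documents do not support that: a preserved share is stable and shifts nothing; only a rising share does so. Nor do they show that the month-24 contrast will be diluted by any particular amount, since CD4 recovery is expected in adolescents generally and the shares may converge.

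**Conclusion.** The point holds in a limited form. The primary reading combines HIV DNA per CD4 cell with the CD4 share of PBMC, and the protocol's own reasoning gives grounds to expect that share to vary by stage and over time. At month 24 the difference between the two scales is log10(early share / control share): 0 to about 0.25 log10 over the assumed shares, and zero if they have converged. When the early share is the higher, the effect runs against the hypothesis; it costs power and understates the contrast, and cannot by itself produce a false benefit of early treatment at that visit. The decay comparison is less predictable: the assumed cases run from +0.176 to −0.074 log10.

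These figures rest on assumed shares and on CD4 cells as the carriers. It would go too far to call the per-PBMC endpoint invalid. It is interpretable, but not alone.

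**What to change.** Keep the per-PBMC endpoint. Pre-specify, as a key supporting analysis, the same models on HIV DNA per million CD4 T cells:

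- CD4 share of PBMC = CD4 count / (lymphocytes + monocytes), from the T cell subsets and the blood count differential of the same visit. The CD4 percentage alone will not serve, because it is usually a share of lymphocytes.
- HIV DNA per million CD4 = (reading per 5 million PBMC / 5) / CD4 share.
- State which quantity reservoir size refers to.
- Report both scales, and interpret with caution where they disagree. Do not make a conclusion conditional on agreement, since that would keep the possibly diluted scale as a gate.
- Do not enter CD4 share as an ordinary covariate, because stage at treatment start affects it.

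No extra blood is needed. Under Table 2 the subsets and differential coincide with the reservoir draws at entry, weeks 2 and 8, and every visit from month 4. The week 1 and week 4 draws have neither in that table, so the per-CD4 series would omit them. The costs are a modest amount of analysis, some added measurement error from the share, and the possibility that the per-CD4 value reads low where the additional CD4 cells are naive.

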### Statistical Considerations

#### Descriptive Statistics

The results of this study will be primarily descriptive. In acute cases, the Fiebig score at the time of initiation of ART and the time to suppression of plasma viremia will be summarized over time as mean (SD). The analyses of immune biomarker assessments follow the same analysis.

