On initial identification of HIV infection, following written informed consent, youth are enrolled into the study, with confirmatory HIV RNA performed as well as a standard HIV fourth generation antigen-antibody assays. Study youth have a clinical visit with history, physical examination, and detailed medical or behavioral questionnaire performed. Youth have HIV genotypic susceptibility testing performed and basic hematologic and chemistry panels assessed. They are evaluated for concurrent infections, including syphilis; hepatitis A, B, and C; chlamydia; gonorrhoea; tuberculosis; and cytomegalovirus (CMV). Potent cART is prescribed at the enrollment visit (according to the standard of care procedures or Department of Health and Human Services [DHHS] guidelines and preferably using a single daily pill), and whole blood is collected to perform tests to determine Fiebig staging [11]. Serial follow-up blood samples are obtained in subsequent visits for HIV biomarkers and to monitor response to cART. The aim was to describe and compare viral dynamics, viral decay, and persistence of viral reservoirs in individuals who are acutely, recently, or chronically infected over time, with results correlated with duration of viral suppression. These assays used to measure these parameters include quantitative HIV RNA PCR; measurement of proviral DNA by digital droplet PCR; and studies of HIV-specific immunity, including cellular immunity, cytotoxic T cell responses, immune activation markers, and HIV neutralizing antibody.

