## Methods

### Design and Population

This is a longitudinal strategic prospective treatment study that identifies, promptly treats, and follows a cohort of adolescent or young adults aged 12 to 24 years who have acute, recent, or established HIV infection. It will measure the effects of early intensive antiretroviral therapy on the establishment and persistence of HIV-1 reservoirs and HIV-1-specific immunity in acutely or recently HIV-infected youth compared with newly diagnosed youth with established infection lasting over 6 months. All youth will be treated according to the standard of care and followed for a period of 24 months.

This study is the first of its kind to enroll a highly at-risk population of HIV-infected adolescents or young adults in the United States. In 2015, among youth aged 13 to 24 years diagnosed in the United States, 81% were gay and bisexual males. Of newly diagnosed male youth, 55% were black, and 24% were Latino [33]. Among youth, an HIV seroprevalence study showed a 5.3% homelessness rate and considered homeless youth to be at highest risk of infection [5]. We have elected to target and enroll youth from 2 HIV epicenters, with large populations of infected and at-risk youth in Los Angeles and New Orleans.

In 2013, a total of 1820 Los Angeles County residents were reported as newly diagnosed with HIV infection, more than that of other urban cities, including Cook County, New York County, Miami-Dade County, and Harris County [34]. Los Angeles contains 6 geographic *hotspots*, which include the following areas: Metro, San Fernando Valley, South Los Angeles, East Los Angeles, San Gabriel, and South Bay [34]. According to a 2015 surveillance report, the New Orleans Metairie area was ranked third based on rate (per 100,000) of HIV diagnosis [33]. The Adolescent Trials Network (ATN) 110 Study in New Orleans screened a total of 200 gay, transgender, and bisexual youth between January and September 2013 and found 9 to be acutely infected, demonstrating the magnitude of the problem in this population [35].

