
Once enrolled, youth will eventually fall into different categories according to the Fiebig Stage Classification System based on WB results (Table 1), which characterizes the progression of HIV-1 infection from exposure to seroconversion. This staging determines acute or recent or established HIV infection status. Enrollment-visit plasma samples (which are before cART initiation) are used to determine Fiebig staging. On the basis of these stages, youth are placed into 1 of 2 cohorts, which can be further divided into groups as shown in Table 1. We expect to enroll 36 youth in each cohort over a 2-year period. Our acutely or recently infected cohort consists of Fiebig stages 1 to 5 and can be identified based on HIV-1 antibody diagnostic profile. Our control cohort consists of individuals in Fiebig stage 6 who are identified by a positive WB with a p31 band.

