Youth will take study medications and come for follow-up visits with physicians at clinic sites for up to 24 months according to the schedule of evaluations (Table 2) for assessment of viral load and HIV reservoir assays, as well as monitoring of coinfections. In addition to the enrollment visit, there will be a total of 9 follow-up visits during which samples will be collected for clinical Laboratoriess and immune reservoir studies. Of the 10 visits, 8 are scheduled during the first 12 months of ART, with 2 subsequent visits performed at 18 and 24 months.

The HIV WB is a part of immune reservoir studies and does not need to be repeated if it shows a full profile Fiebig stage 6 until 1 year. If subjects cannot do both a 2-week and 4-week follow-up visit, it is acceptable to combine the 2 visits into 1 as long as all clinical laboratory assays specified for week 4 are taken. The window periods (not shown in table) are as follows: −7 days for screen; ±7 days for week 1; ±14 days for weeks 2 and 4; ±7 days for week 8; and ±14 days for 4, 8, 12, and 24 months. In the event of virologic failure (not shown in table), HIV-1 genotypic testing will be conducted. In the event of premature study or treatment discontinuation (not shown), our team will try to collect HIV-1 genotypic testing, T cell subsets, HIV RNA quantitative assay, and 30 mL for immune reservoir studies.

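### Time to viral suppression is to be summarised as mean (SD), which does not suit a time that is censored and seen only at visits

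*Protocol article*

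**What the plan says.** The Descriptive Statistics section calls the results primarily descriptive. Its sentence on this outcome opens with "In acute cases, the Fiebig score at the time of initiation of ART" and continues that "the time to suppression of plasma viremia will be summarized over time as mean (SD", so one mean (SD) is prescribed for both the Fiebig score and the time to suppression.

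Other sections show what kind of variable this is:

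- **Some youth will not reach the event.** The text after Table 2 provides for a change of regimen and adds: "The same will occur with subjects who do not achieve viral load remission". Study Aims expects some youth to stop or interrupt therapy. Immune Reservoir Studies anticipates loss to follow-up, and Regression Analysis models drop-out as a binary outcome.
- **The event is seen only at visits.** The Table 2 row "HIV-1 RNA PCR^e^ quantitative" is marked at entry, weeks 2 and 8, and months 4, 8, 12, 18 and 24. Windows are ±"7 days for week 1; ±14 days for weeks 2 and 4; ±7 days for week 8". The visit descriptions differ from the table: they also list viral load testing at day 7 and HIV-1 RNA PCR at week 4.
- **A comparison is intended.** Study Aims says "The aim was to describe and compare viral dynamics, viral decay, and persistence of viral reservoirs in individuals who are acutely, recently, or chronically infected". Immune Reservoir Studies and Regression Analysis plan comparisons of viral dynamics and of follow-up results by Fiebig stage, using linear or logistic longitudinal models.

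**The concern.** A mean needs a value for every person in it. Youth who never suppress, or who leave first, have none, so they must be left out or given an invented time. If they are left out, the mean describes only the successes and looks the same whether few or many fail. That matters in a population where the protocol itself expects interruption and drop-out. Taking the visit date as the event date adds upward bias that depends on the spacing of visits.

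As worded, the summary covers acute cases, while the stated aim is to compare acute, recent and chronic infection.

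The Fiebig score is ordinal, with unequal time bands in Table 1 (0-20, 20-30 and 30-90 days for the first three groups). A mean of 3 could be all stage 3 or an even mix of stages 1 and 5.

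**Working it through.** The article gives no expected suppression time, suppression rate or drop-out rate for this study, so there is no stated figure to reproduce. The check is illustrative.

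**Inputs from the protocol article**
- 36 youth per cohort ("We expect to enroll 36 youth in each cohort over a 2-year period") and 24 months of follow-up ("All youth will be treated according to the standard of care and followed for a period of 24 months").
- RNA visits from Table 2, in weeks: 2, 8, 17.4, 34.8, 52.2, 78.3, 104.4. The gaps are 2, 6, 9.4, 17.4, 17.4, 26.1 and 26.1 weeks.
- The cited phase 2 trial in the Treatment section: 99/112 = 88.4% below 50 copies/mL at 48 weeks, so about 12% not suppressed.

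**Assumed inputs**
- Lognormal time to suppression in those who suppress, log-SD 0.8, median 4, 8 or 12 weeks.
- Share never suppressing: 0%, 12% or 30%, independent of timing in the others. The cited 12% is a 48-week figure from another study and is borrowed only for scale.
- Drop-out over two years: 0% to 30%.

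**Step 1: mean dated at the visit.** With F(t) = Φ(ln(t/8)/0.8), the values of F at the seven visits are 0.0416, 0.5000, 0.8343, 0.9669, 0.9905, 0.9978 and 0.9993. The probabilities of first being seen suppressed at each visit are the differences: 0.0416, 0.4584, 0.3343, 0.1327, 0.0235, 0.0073 and 0.0015. Multiplying each by its visit week and adding:

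0.083 + 3.668 + 5.817 + 4.616 + 1.228 + 0.575 + 0.158 = 16.145

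Divided by 0.9993, this is 16.2 weeks. The true mean in those who suppress is 8 × exp(0.8²/2) = 11.0 weeks.

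Simulation with 36 youth gives the same picture, with all suppressing and no drop-out:

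| Median in suppressors (weeks) | True mean | Mean, Table 2 visits | Mean, with RNA at weeks 1 and 4 added |
|---|---|---|---|
| 4 | 5.5 | 9.3 | 8.0 |
| 8 | 10.9 | 16.1 | 15.5 |
| 12 | 16.1 | 22.4 | 22.2 |

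**Step 2: response to failure.** If a share p never suppresses, the median over all youth solves (1 − p)F(t) = 0.5, so t = 8 × exp(0.8 × z), where z is the normal quantile of 0.5/(1 − p).
- p = 0: z = 0, t = 8.0 weeks.
- p = 0.12: 0.5/0.88 = 0.568, z = 0.172, t = 9.2 weeks.
- p = 0.30: 0.5/0.70 = 0.714, z = 0.566, t = 12.6 weeks.

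The share p does not enter the expected mean of Step 1. Across the simulated combinations of p and drop-out, that mean stays between 15.7 and 16.2 weeks. Drop-out lowers it slightly, because late suppressors are more often lost.

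**Step 3: how many have no value.** At 12%, 36 × 0.12 = 4.3 youth. With 12% never suppressing and 20% drop-out, about 5 to 6 of 36. With 30% never suppressing and 20-30% drop-out, about 11 to 13.

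**The case against.** The strongest reply has five parts.

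- **Two of the consequences are not written down.** A reader might infer that the plan excludes non-suppressors and drop-outs and takes the visit date as the event date. The article states neither rule, and a full analysis plan could handle both. This stands as to wording: they are consequences of a plain mean on this schedule. It does not rescue the mean, because a proper censoring rule would have to replace mean (SD), which is what the article fixes.
- **Controls are not left without any comparison.** A reader might infer that they are. Study Aims, Immune Reservoir Studies and Regression Analysis plan comparisons across Fiebig stages, and stage 6 is the control cohort. This stands. What remains is narrower: no comparison of time to suppression itself is named, and the listed models do not fit a censored time.
- **The restriction to acute cases is ambiguous.** The opening phrase is natural for the Fiebig score, which is always 6 in controls, and may not be meant to govern the second item. This stands as a doubt about intent.
- **The visit text lists more RNA tests than Table 2.** With weeks 1 and 4 added, the inflation shrinks, mostly when suppression is fast, but remains.
- **The sizes rest on assumed rates.** They do. The flatness of the mean also relies on failure being independent of timing in the others. At the 12% borrowed from the cited trial, the median moves only from 8.0 to 9.2 weeks; the larger shift needs 30%.

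**Conclusion.** The point holds in this form: mean (SD) is an unsuitable stated summary for a time that is right-censored by non-suppression and loss and interval-censored by the visit schedule. With a median of 8 weeks in suppressors, the mean stays near 16 weeks while the median over all youth runs from 8.0 to 12.6 weeks. About 4 of 36 youth would have no value at 12% non-suppression, and 11 to 13 at the upper end of the assumed range. These sizes are illustrative. That a mean over observed suppressors leaves out the failures does not depend on them.

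It should be fixed, but a reader might infer that it undermines the study's main result, and the article does not support that. The primary endpoint is cell-associated HIV-1 DNA at 24 months, and no stated sample size or decision rule uses this mean.

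**What to change.** - Replace mean (SD) with a Kaplan-Meier or interval-censored estimate of time from ART start to first HIV RNA below a named suppression limit, in both cohorts. Censor youth not suppressed or lost at their last RNA.
- Report the median, and the proportion suppressed at fixed visits with confidence intervals. If the cohorts are to be compared on this outcome, name a method that handles censored times.
- Report Fiebig stage as counts per group.
- Reconcile Table 2 with the visit descriptions on HIV RNA at weeks 1 and 4, since the censoring intervals depend on it.

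This changes analysis wording and uses data already collected. The cost is slightly more analysis work, and intervals will be wide with about 36 youth per cohort.
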